## Abstract

**Background:**

Lung cancer is the leading cause of cancer death worldwide and characterized by a poor prognosis. It has a major impact on the psychological wellbeing of patients and their partners. Recently, it has been shown that Mindfulness-Based Stress Reduction (MBSR) is effective in reducing anxiety and depressive symptoms in cancer patients. The generalization of these results is limited since most participants were female patients with breast cancer. Moreover, only one study examined the effectiveness of MBSR in partners of cancer patients. Therefore, in the present trial we study the effectiveness of MBSR versus treatment as usual (TAU) in patients with lung cancer and their partners.

**Methods/Design:**

A parallel group, randomized controlled trial is conducted to compare MBSR with TAU. Lung cancer patients who have received or are still under treatment, and their partners are recruited. Assessments will take place at baseline, post intervention and at three-month follow-up. The primary outcome is psychological distress (i.e. anxiety and depressive symptoms). Secondary outcomes are quality of life (only for patients), caregiver appraisal (only for partners), relationship quality and spirituality. In addition, cost-effectiveness ratio (only in patients) and several process variables are assessed.

**Discussion:**

This trial will provide information about the clinical and cost-effectiveness of MBSR compared to TAU in patients with lung cancer and their partners.

**Trial registration:**

ClinicalTrials.gov NCT01494883.

## Background

With an estimated 1.4 million deaths per year, lung cancer is the leading cause of death by cancer worldwide. Even with the best available treatment, five-year survival is merely 16% and about 60 to 70% of patients die within the first year after diagnosis [1]. This poor prognosis is often caused by a late diagnosis as the presentation usually occurs when the lung cancer is advanced. Patients may develop burdensome symptoms like pain, dyspnoea, fatigue and cough and they may undergo radical treatment, including surgery, chemo- and radiotherapy. Not surprisingly, lung cancer has a major impact on the psychological wellbeing of patients and their family. Akechi and colleagues [2] showed that 19% of patients with advanced lung cancer meets the criteria of psychiatric disorders, especially depressive and adjustment disorders. Of patients who had been successfully treated for lung cancer 15% met the criteria for a minor or major depressive disorder [3]. The prevalence rate of depressive and anxiety symptoms among lung cancer patients ranges from 20 to 47% [4-7]. Compared to patients with other cancer diagnoses, lung cancer patients report the highest rates of distress (43 to 58%) [8,9] resulting in a lower quality of life [10].

Family, friends and especially partners of patients with lung cancer also have to deal with its psychological impact [11-14]. Partners not only provide emotional and practical support, they also have to cope with their own concerns, including the uncertainty regarding the course of the illness and the fear of losing their partner [15]. More than 50% of partners of lung cancer patients report negative emotional effects of caregiving [16]. Around 40% of partners of patients with advanced lung cancer report high levels of distress [17]. The relationship between patient and partner can also be affected by the cancer. It has been shown that some partners report a lower quality of their relationship after the diagnosis of lung cancer [18].

Though numerous studies examined the psychological distress of lung cancer patients and their partners [2-22], not much research is done on how to alleviate distress in these groups [23]. In addition, the available studies on managing the psychosocial care needs of cancer patients and their families have focused on care at the very end of life (e.g. [24-26]). Recently, studies have demonstrated that palliative care initiated early in treatment improves the quality of life and depressive symptoms of lung cancer patients [10,27]. This stresses the importance of integrating psychosocial care for lung cancer patients and their partners early in the treatment, rather than instigating it once life-prolonging therapies fail.

In the past ten years MBSR has become a promising psychosocial intervention for cancer patients. Mindfulness is defined as intentionally paying attention to moment-by-moment experiences in a non-judgmental way [28]. MBSR is an 8-week group-based training consisting of meditation practices, such as the bodyscan, gentle yoga, sitting and walking meditation. By repeatedly bringing attention back to the current experience, participants gradually learn to disengage from dysfunctional thoughts and directly experience the emotions and bodily sensations of the present moment. MBSR aims to provide participants with the ability to step back from ruminating about the past or worrying about the future and simply allow experiences to unfold [28,29]. A recent meta-analysis [30] of 13 nonrandomized studies and 9 randomized controlled trials (RCT) concluded there is positive evidence for the use of mindfulness-based interventions in reducing psychological distress in cancer patients. Among the RCT’s, a reduction in symptom severity was found for both anxiety and depression corresponding to moderate pooled controlled effect sizes (Hedges’s *g =* 0.37 and Hedges’s *g* = 0.44, respectively) [30]. Though mindfulness-based interventions seem to be effective, the authors note that across studies the majority of participants were women (85%) and diagnosed with breast cancer (77%). Compared to breast cancer patients, patients with lung cancer are more often male, older and have a poorer prognosis. Furthermore, of these 22 studies only one study included the partners of the patients showing that partners also benefit from the MBSR training [31]. This is quite surprising since partners of cancer patients also report high levels of distress [32].

### Aims

The aim of the Mindfulness for Lung Oncology Nijmegen (MILON) study is to examine the effectiveness of MBSR compared to TAU in reducing psychological distress in patients with lung cancer and their partners. We hypothesize that patients in the MBSR group will report a lower level of psychological distress (i.e. anxiety and depressive symptoms), higher levels of quality of life, quality of relationship and spirituality than those in the TAU group. Medical and societal costs will be lower in the MBSR versus TAU group. We expect partners in the MBSR group to report a lower level of psychological distress and higher levels of caregiver appraisal, relationship quality and spirituality than their counterparts in the TAU group. With regard to the working mechanisms of the MBSR programme, we will examine changes in mindfulness skills, self-compassion, rumination, intrusion, avoidance and adherence to MBSR.

## Methods/Design

### Study design

The design of the ‘MILON’ study is a parallel group randomized controlled trial with an embedded process study. Participants are randomized between MBSR and TAU. The study protocol has been approved by our ethical review board (CMO Arnhem-Nijmegen) and registered under number 2011–519.

### Participants and procedure

Patients and partners are recruited at the outpatient clinic of the Department of Pulmonary Diseases, Radboud University Nijmegen Medical Centre (RUNMC) by a nurse practitioner and the attending physician. Patients and partners are invited to participate together but both are welcome to participate on their own if they do not have a partner or their partner is not willing to participate. Patients and/or partners who are interested are provided with an information leaflet. If they are willing to participate, they are invited for a research interview, in which in- and exclusion criteria are assessed and informed consent is taken.

At other participating hospitals (Department of Pulmonary Diseases, Canisius-Wilhelmina Hospital, Nijmegen; Department of Pulmonary Medicine, Rijnstate, Arnhem; Department of Oncology, Elkerliek Hospital, Helmond; Department of Pulmonary Medicine, Jeroen Bosch Hospital; Department of Pulmonary Diseases, Maas hospital Pantein, Boxmeer) patients and their partners will be sent a letter with the invitation to participate in the study. One week later the researcher calls the patients to answer possible questions and asks whether the patient and partner are interested in participation. If so, they are invited for a research interview at the RUNMC.

#### Eligibility

We include patients and/or partners of patients, who are (a) diagnosed with cytologically or histologically proven non-small cell lung cancer or small cell lung cancer and (b) have received or are still under treatment. Exclusion criteria for both patient and partner include: (a) being under 18 years of age, (b) not being able to understand or use the Dutch language, (c) former participation in MBSR or Mindfulness-Based Cognitive Therapy (MBCT), (d) current and regular treatment by psychologist or psychiatrist, (e) current participation in other psychosocial programme and (f) physical or cognitive (<26 on the Mini-Mental State Examination (MMSE)) impairments hampering participation in MBSR training or completion of questionnaires.

#### Baseline

Patients and partners are interviewed to obtain demographics and clinical characteristics, after which they are screened for cognitive impairments with the MMSE [33]. After that, baseline questionnaires, including the Distress Thermometer (DT) [34,35], are administered, followed by randomization. Table 1 shows the assessment instruments and time points at which the questionnaires are administered to patients and partners.

**Table 1 T1:** Measurements and corresponding time points for patient and partner

**Measure**	**Target**	**T0**		**T1**		**T2**	
		**pt**	**pr**	**pt**	**pr**	**pt**	**pr**
MMSE	Cognitive impairments	x	x				
DT	General distress	x	x				
HADS	Psychological distress	x	x	x	x	x	x
QLQ-C30	Quality of life	x		x		x	
QLQ-LC13	Quality of life	x		x		x	
SIP	Impact of sickness	x		x		x	
SPPIC	Caregiver burden		x		x		x
CRA-SE	Caregiver self-esteem		x		x		x
IMS-S	Relationship satisfaction	x	x	x	x	x	x
MIS	Communication about cancer	x	x	x	x	x	x
SAIL	Spirituality	x	x	x	x	x	x
FFMQ	Mindfulness skills	x	x	x	x	x	x
SCS	Self-compassion	x	x	x	x	x	x
RRS-EXT	Rumination	x	x	x	x	x	x
IES	Psychological stress reaction	x	x	x	x	x	x
Diary	Health care use, work absence	Monthly during study period for pt					
Calendar	Mindfulness adherence	Monthly during study period for pt and pr					

*Note.* T0 = Baseline measurement; T1 = Post-intervention measurement; T2= 3-month follow-up measurement; pt = Patient; pr = Partner; MMSE = Mini Mental State Examination; DT = Distress Thermometer; HADS = Hospital Anxiety and Depression Scale; QLQ-C30 = Quality of Life – Cancer; QLQ-LC13 = Quality of Life – Lung Cancer; SIP = Sickness Impact Profile; SPPIC = Self-Perceived Pressure from Informal Care; CRA-SE = Caregiver Reaction Assessment – Care-Derived Self-Esteem; IMS-S = Investment Model Scale-Satisfaction; MIS = Mutuality and Interpersonal Sensitivity; SAIL = Spiritual Attitude and Involvement List; FFMQ = Five Facet Mindfulness Questionnaire; SCS = Self-Compassion Scale; RRS-EXT = Rumination Response Scale – Extended Version; IES = Impact of Event Scale.

#### Randomization

Randomization is stratified according to setting and minimized for (a) stage of disease (curative *versus* palliative), (b) baseline level of anxiety and depressive symptoms (anxiety or depression subscale score of Hospital Anxiety and Depression Scale (HADS) <8 *versus* ≥8), (c) treatment during MBSR (no treatment *versus* chemo- and/or radiotherapy) and (d) participation (patient alone *versus* partner alone *versus* patient and partner together). Randomization is computerized, using a randomization website, specifically designed for this study, on which the researcher can fill out the required data. The researcher communicates treatment allocation to the nurse practitioner, who informs the patient and/or partner.

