#### Primary analyses

The samples of lung cancer patients and partners will be analyzed separately. Baseline characteristics of the population will be compared between MBSR and control group to ensure that key variables were evenly distributed by randomization. First, analyses will be based on the intention-to-treat approach. Next, we will perform per-protocol analyses with the treatment-adherent sample (i.e. in the MBSR condition participants have to attend at least four of the eight MBSR sessions [73] and in the TAU condition participants do not attend a mindfulness-based programme).

We will use linear mixed models to analyze all outcome variables (i.e. psychological distress, quality of life (only for patient), caregiver appraisal (only for partner), relationship quality and spirituality), with treatment as fixed factor, baseline measurement as covariate and a random intercept based on MBSR group. This procedure will use all observed data in our analyses. In addition, Cohen’s *d* effect size [74] will be reported based on the difference between the group means on baseline and follow-up scores, divided by the pooled standard deviation at baseline and follow-up.

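### The outcome model leaves out setting and most of the minimisation factors; if these are prognostic beyond baseline, the test is conservative and some precision is forgone

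*Protocol article*

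**What the plan says.** Under Randomization, the protocol article states: "Randomization is stratified according to setting and minimized for (a) stage of disease" (curative or palliative). The other minimisation factors are the baseline HADS category (below 8, or 8 and above, on a subscale), treatment during the MBSR period (none, or chemo- and/or radiotherapy) and participation (patient alone, partner alone, or both). The researcher enters these data on the randomisation website.

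Under Primary analyses: "We will use linear mixed models to analyze all outcome variables", specified as "with treatment as fixed factor, baseline measurement as covariate and a random intercept based on MBSR group". Also: "The samples of lung cancer patients and partners will be analyzed separately". The only other baseline step is this: "Baseline characteristics of the population will be compared between MBSR and control group to ensure that key variables were evenly distributed by randomization".

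No other section says that the allocation factors enter the model.

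**The concern.** Forcing balance on prognostic factors reduces the true sampling variance of the treatment difference. A model without those factors leaves their contribution in the residual, so its standard error reflects a variability that the allocation has already removed. Confidence intervals are then too wide and the test rejects too rarely.

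For the HADS total, the continuous baseline score largely covers the HADS minimisation factor; setting and the other three factors are uncovered. For the other outcomes the covariate is that outcome's own baseline, so setting and all four minimisation factors are uncovered. The random intercept does not stand in for setting, because it is defined by the training group.

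At stake is precision in a trial that needs 88 evaluable patients and whose Discussion expects recruitment to be a challenge.

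**Working it through.** **1. The plan's own figure.** Inputs from the Sample size section: two-sided alpha 0.05, power 80%, effect size 0.5, 64 per group, cluster size 7, ICC 0.01, correlations 0.8 and 0.5, drop-out 20%.

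- Power of the t-test at 64 per group (noncentral t): 0.801.
- Clustering: 1 + (7 − 1) × 0.01 = 1.06.
- Repeated measures and baseline: (1 + 0.8)/2 − 0.5² = 0.65.
- 64 × 1.06 × 0.65 = 44.1, given as 44 per arm, or 88; 88/0.8 = 110.

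The sample size reproduces and is not at fault.

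**2. Effect of the omission.** Let R² be the share of residual variance, after the baseline score, that the omitted factors explain. The article does not give it, so a range is assumed. With exact balance, and a non-centrality of 1.96 + 0.84 = 2.80 for 80% power:

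- ratio of model SE to true SE = 1/√(1 − R²)
- type I error, factors omitted = 2 × [1 − Φ(1.96/√(1 − R²))]
- power, factors omitted = Φ((2.80 − 1.96)/√(1 − R²))
- power, factors included = Φ(2.80/√(1 − R²) − 1.96)

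| Assumed R² | SE too large by | Type I error, omitted | Power, omitted | Power, included | Power forgone (points) |
|---|---|---|---|---|---|
| 0 | 0% | 5.0% | 80.0% | 80.0% | 0 |
| 0.05 | 2.6% | 4.4% | 80.6% | 82.0% | 1.4 |
| 0.10 | 5.4% | 3.9% | 81.2% | 84.0% | 2.8 |
| 0.20 | 11.8% | 2.8% | 82.7% | 87.9% | 5.2 |

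Worked line for R² = 0.20: √0.80 = 0.894; 1.96/0.894 = 2.19, two-sided tail 0.028; 0.84/0.894 = 0.94, Φ = 0.827; 2.80/0.894 − 1.96 = 1.17, Φ = 0.879.

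**3. Simulation check.** 88 patients were allocated by minimisation on five factors (setting with three levels, the rest with two) and analysed by ANCOVA on baseline, with and without setting, stage, treatment and participation. There were 1000 runs per scenario, so the Monte Carlo error of a 5% rate is √(0.05 × 0.95/1000) ≈ 0.007. Clustering and drop-out were not simulated.

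| R² | Type I error, omitted / included | Power, omitted / included | Mean model SE under the null, omitted / included |
|---|---|---|---|
| 0 | 0.064 / 0.059 | 0.832 / 0.816 | 0.172 / 0.173 |
| 0.10 | 0.042 / 0.056 | 0.805 / 0.826 | 0.171 / 0.163 |
| 0.20 | 0.028 / 0.049 | 0.828 / 0.881 | 0.172 / 0.154 |

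At R² = 0.20 the planned model reported a mean SE of 0.172 under the null, against an empirical 0.153, in line with the formula. At R² = 0.10 both type I error rates are within simulation noise of 5%. At R² = 0 the two models have practically the same SE, and both rates lie within about two Monte Carlo errors of 5%.

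**The case against.** **The model sentence may be condensed.** It names no time term and no participant-level effect, although the sample size assumes repeated post-treatment measurements, so it may not list every term. The full protocol or analysis plan might add covariates. This part stands: the article does not say that the factors will be left out on purpose. It does, however, name the covariate, and names only one, so the model as published needs the correction.

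**The harm is conditional.** A reader might infer that the standard errors are simply too large. The article does not support that: it gives no figure for how prognostic the factors are beyond baseline, and for the primary outcome the closest factor is already covered by the continuous HADS score. The article's link between advanced disease and distress makes some prognostic value plausible, but does not size it.

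**The figures are upper bounds for each R².** Minimisation balances the units allocated, including partners taking part alone. Patients and partners are analysed separately, and 20% drop-out is expected. Balance among those analysed will be looser than the formula assumes, so the fall in type I error will be smaller.

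**The baseline comparison.** One might read it as the plan's substitute for adjustment. The text says only that characteristics will be compared. It does adjust nothing, but it is not offered as a replacement.

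**Conclusion.** The point holds as a conditional loss of efficiency. As published, the model omits setting, stage, treatment during MBSR and participation for every outcome, and the HADS category as well for non-HADS outcomes. Under an assumed residual R² of 5% to 20% and exact balance, the cost is a standard error up to about 3% to 12% too large, a type I error as low as 4.4% to 2.8%, and about 1 to 5 points of power. At R² = 0 the cost is nil.

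Two stronger readings should be set aside. The omission does not make the trial underpowered: with the factors left out, calculated power stays at or above the planned 80% throughout the range. Nor does it put a positive result in doubt, because the error is conservative. The change is worth making because it is nearly free, not because the planned analysis is invalid.

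**What to change.** In Primary analyses, add to every outcome model, as fixed covariates with the values entered at randomisation:

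- setting, as defined in the randomisation system, with sparse settings pooled by a rule set before analysis;
- stage (curative or palliative);
- treatment during MBSR (none, or chemo- and/or radiotherapy);
- participation, which has two levels (alone or together) within each separate patient or partner analysis.

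For non-HADS outcomes, also add the HADS category. Using the value entered at randomisation matters here, because the article does not say whose score sets the category for a couple. Keep the baseline comparison descriptive, so that it does not prompt a later choice of covariates.

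**Cost.** A few degrees of freedom. The article does not define setting. If it means hospital, six are listed, or about 88/6 ≈ 15 evaluable patients each, and the adjustment uses 5 + 1 + 1 + 1 = 8 degrees of freedom before pooling (9 with the HADS category). In the simulation with three settings and non-prognostic factors, the model SE rose only from 0.172 to 0.173. No new data are needed and the sample size need not change.

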#### Follow-up assessments

Follow-up assessments take place post intervention and at three-month follow-up. Participants who have access to the internet and have an email address receive the questionnaires online. If not, they receive the questionnaires on paper along with a reply envelope. In case of drop-out, the researcher tries to contact the participant by phone to complete a minimum set of outcome measures and to identify the main reason for drop-out.

### Intervention

The MBSR curriculum used is primarily based on the Mindfulness-Based Stress Reduction programme as developed by Kabat-Zinn [28] but contains some elements of the MBCT programme by Segal, Williams and Teasdale [29], like psycho-education on the interrelatedness of feelings and thoughts. Moreover, some modifications have been made to make the intervention more suitable for patients with lung cancer and their partners, such as psycho-education about grief [36]. In addition, a mindful communication exercise in which partners talk with each other about the cancer was added. The programme consists of 8 weekly 2.5-hour sessions, a silent day between session six and seven and home practice assignments of about 45 minutes, 6 days per week. Participants receive a set of CDs with guided mindfulness meditation exercises for home practice and a folder with information and home practice instructions for the forthcoming week. Table 2 shows the content of the MBSR programme per session. The MBSR courses are taught by mindfulness teachers with extensive training in MBSR. They all fulfil the advanced criteria of the Center for Mindfulness of the University of Massachusetts Medical School [37] and maintain a regular personal meditation practice. Teachers were trained, supervised and assessed to ensure their competency levels met the qualification criteria to instruct the MBSR classes. During the trial, teachers will receive weekly supervision and a number of sessions will be videotaped to evaluate competence and adherence with the Mindfulness-Based Interventions – Teaching Assessment Criteria [38].

**Table 2 T2:** Content of MBSR programme per session

**Theme of session**	**Meditation exercise**	**Didactic teaching**	**Homework**
1. Automatic pilot	- Bodyscan	- Intention of participating	- Bodyscan
		- Raisin exercise	- Eating one meal mindfully
			- Attention for routine activity
2. Mindfulness of the breath	- Bodyscan	- Imagery exercise to demonstrate relationship between thoughtsand feelings	- Bodyscan
	- Sitting mediation with focus on breath		- Attention for breath
			- Awareness of pleasant events
			- Attention for routine activity
3. Observing limits	- Yoga while lying down	- Seeing exercise to demonstrate difference between observation and interpretation	- Bodyscan or yoga
	- 3-min breathing space		- Sitting meditation
			- Awareness of unpleasant events
			- 3-min breathing space
4. Opening up to distress	- Sitting mediation with focus on breath, body and sound	- Interrelatedness of feelings, thoughts and bodily sensations	- Bodyscan or yoga
			- Sitting meditation
	- 3-min breathing space	- Psychoeducation about grief	- Awareness of stress reactions
			- 3-min breathing space
5. Responding to distress	- Sitting mediation with focus on breath, body, sound, thoughts, difficulty	- Reacting versus responding	- Meditation by choice
		- Coping with grief	- Awareness of reaction in difficult situation
	- Walking meditation		- Awareness of communication difficulties
	- 3-min breathing space		- 3-min breathing space
6. Mindful communication	- Yoga in standing position	- Mindful communication exercise about effect of lung cancer with their own partner	- Sitting meditation or yoga
	- 3-min breathing space		- Awareness of communication
			- 3-min breathing space during stress
Silent day	- Varying meditation exercises		
	- Silent lunch and tea break		
7. Taking care of yourself	- Sitting meditation ending in choiceless awareness	- Exercise on taking care of yourself by examining how to improve balance in life	- Meditation without CD
	- Yoga or walking meditation		- Reflect on training
	- 3-min breathing space		
8. The rest of your life	- Bodyscan	- Reflection on training	- Further sources of information
	- Short sitting meditation	- Maintaining practice	

